## Abstract

**Background:** The pediatric population with chronic suppurative lung diseases (CSLDs) presents with a clinical profile of persistent productive cough and impaired airway clearance, which leads to reduced exercise capacity and physical activity (PA). The main objective of this research is to evaluate the effect of a 12-week intervention that combines airway clearance techniques (ACTs) and exercise training delivered through synchronous (videoconferencing) and asynchronous implementation at home, supported by an informative, specially designed website and supervised by a physiotherapist on exercise capacity. The secondary objective is to assess adherence to the ACT performance. The hypothesis of the study is that this hybrid tele-rehabilitation program will improve functional and exercise capacity, as well as compliance with ACTs, compared to the usual care. **Methods**: Thirty-two children with CSLDs (other than cystic fibrosis) will be randomly assigned to either the intervention group (home-based, synchronous, and asynchronous ACTs and exercise training) or the control group (usual care). An assessor blind to group allocation will measure the modified shuttle walk test, 6-minute walking test, Chester step test, respiratory muscle strength, handgrip, pulmonary function, PA, sedentary behavior, and quality of life at baseline, at the end of the intervention (3 months), and 6 months after completion. **Discussion**: This study introduces a hybrid (synchronous and asynchronous) tele-rehabilitation program, aiming to improve physical capacity and adherence to physiotherapy management for pediatric CSLD populations.

## 1. Introduction

Chronic suppurative lung diseases (CSLDs) are increasingly recognized as significant contributors to pediatric respiratory morbidity. Within the CSLD’s spectrum, conditions such as protracted bacterial bronchitis (PBB), primary ciliary dyskinesia (PCD), and non-cystic fibrosis bronchiectasis (NCFB) are clinically unified by the hallmark symptom of chronic wet cough [1]. The prevalence of these disorders is highly contingent on diagnostic access and socioeconomic factors. In European populations, the estimated annual incidence ranges from 0.2 to 2.3 per 100,000 children, whereas non-European cohorts show a higher prevalence of approximately 13.3 to 15 per 100,000 [2]. This disparity is most pronounced in indigenous populations, where the prevalence fluctuates between 4.8 and 18.3 per 100,000 cases in New Zealand, Alaska, Australia, and Canada [2].

The growing recognition of the global burden of CSLDs in children has exposed significant inequities in resources and a lack of standardized management across health settings. To address these deficiencies, a recent international consensus established a rigorous set of quality standards to enhance pediatric patients’ quality of life. Individualized airway clearance techniques (ACTs) provided by a respiratory physiotherapist specialist are integral to these quality statements, as ACTs are considered a cornerstone of comprehensive CSLD management [3]. Moreover, the international roadmap of clinical priorities has revealed that access to physiotherapy and expertise in home-based equipment use are among the highest-rated needs expressed by children and their parents [4].

However, traditional delivery models often face substantial barriers, such as geographical distance and high treatment burdens, which can lead to suboptimal adherence and limited access to specialized expertise. While experts have suggested that digital health services may facilitate accessibility, there remains a critical requirement for evidence-based strategies to substantiate and refine the clinical utility of remote interventions within this population [5].

Digital health services (DHSs) cover a broad range of technologies for healthcare delivery, including telehealth (remote care), mHealth (mobile apps), remote patient monitoring (device data tracking), and digital therapeutics (software-driven interventions), aiming to enhance clinical outcomes [6]. In detail, they target compliance with the ACTs [7], the supervision of tailored exercise regimens [8,9,10,11,12,13], and the dissemination of structured patient education [14].

Building on the diverse utility of DHSs, a recent systematic review has rigorously evaluated the efficacy of delivering structured exercise programs via DHSs in children and adolescents with CSLDs [15]. Diverse interfaces, including active video games (*n* = 3), videoconferencing (*n* = 3), and digital spirometry (*n* = 1), were used to deliver and monitor exercise regimens in either in-person, remotely supervised at the clinic, or at-home settings in a pediatric population aged between 9 and 20 years old. A meta-analysis revealed a statistically significant improvement in the 6-minute walk test distance, with a pooled mean difference of 37.2 m, in favor of the eHealth group compared to the control group, who received the usual care [15]. However, studies included in this systematic review mainly referred to the pediatric population with cystic fibrosis (5 out of 7), highlighting the scarcity of the literature in other CSLD populations, such as PCD, PBB, or NCFB.

Adherence to ACTs remains a key component of disease management. Despite its clinical significance, the evaluation of adherence is limited, with the existing literature predominantly focused on pediatric cohorts with cystic fibrosis (CF). Available data indicate that adherence rates for unsupervised, home-based ACTs are consistently low [16]. Geographical distance from specialized physiotherapy centers constitutes a significant determinant of healthcare utilization and accessibility in physiotherapy [16]. Despite the increasing use of DHSs, there are no randomized controlled trials (RCTs) specifically targeting ACT adherence and access to care in CSLD populations other than those with CF.

This study aims to investigate the effects of applying digital physiotherapy services in the management of specific clinical outcomes in children with chronic suppurative lung diseases other than cystic fibrosis. We hypothesize that a hybrid (synchronous and asynchronous) tele-rehabilitation program that includes exercise training and ACTs can improve functional and exercise capacity, as well as compliance with ACTs, compared to the usual care. From the range of available DHSs, this study employed live videoconferencing sessions and an informative website.

## 2. Materials and Methods

### 2.1. Study Design

This is a prospective, single-center, two-arm (1:1), assessor-blinded, randomized controlled clinical trial that aims to recruit 32 children from the outpatient clinic of the third Pediatric Pulmonology Unit, “Attikon” University Hospital of Athens in Greece, between May 2026 and May 2027. To account for the geographical dispersion of patients across remote regions of Greece, the collection of medical histories will be conducted via a 40 min synchronous videoconference session through Microsoft Teams. Afterwards, all child–parent/caregiver dyads will attend a 40 min, in-person session with the physiotherapist at the outpatient clinic. This session is designed to provide standardized training on ACTs for subsequent implementation at home, as part of the usual care. Then, children will be randomized into parallel arms: the digital health services group (DHSG) and the control group (CG). All clinical assessments (baseline, post-intervention, follow-up) will be conducted in-person at the outpatient clinic by blinded healthcare professionals. All children will receive the usual care, including inhaled antibiotics and/or bronchodilators for respiratory infections, alongside recommendations to maintain regular physical activity and to perform ACTs at home. The DHSG will undergo a 12-week home-based hybrid (synchronous and asynchronous), remotely administered exercise program and ACTs. Likewise, the DHSG will have access to a specifically designed website about disease management (www.fysao.gr) [17]. Prior to the intervention, parents/caregivers in the DHSG will participate in a 1 h guidance session to ensure proficiency with the use of the VSee Clinic web platform (Vsee Lab, Inc., San Jose, CA, USA). VSee was selected for this study due to its secure, high-resolution videoconferencing software, ease of use, and the fact that it does not need a software system installation. The study process is presented in Figure 1. This protocol follows the Standard Protocol Items: Recommendations for Interventional Trials (SPIRIT) 2025 (Table 1) [18], and ethical approval has been provided by the Physiotherapy department of the University of Thessaly (ID-22510/2025) and the University Hospital of Athens “Attikon” (ID-517/2025) Clinical Research Ethics Committees. The protocol has been registered at ClinicalTrials.gov under identifier NCT07376187, submitted on 28/1/2026.

### 2.2. Randomization

To ensure blinding, an external individual who is not involved in the study will allocate participants randomly to each group using the randomizeR—R package, Version 1.4.2 (RWTH Aachen University, Aachen, Germany) (1:1 simple randomization), executed on an Apple macOS system [19], and will prepare the concealed opaque envelopes that will be given to the participants. Due to the nature of the study, the participants cannot be blinded. However, the study physiotherapist who will assess outcome measures, as well as the researcher who will perform the data analysis, will be blinded to participants’ group allocation.

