Building upon a previous study in children with CF [11], our research team designed an exercise program based on the 24-letter Greek alphabet, where each letter represents an individual aerobic or strengthening exercise, selected so that they can be implemented easily in an online setting at home with minimal equipment. For example, the Greek letter “A” represents the exercise “ALMA”, meaning jumping up and down. In order to adapt the exercise program to age-specific needs and capabilities, the exercises have been modified for two age groups: 6–9 and 10–12 years old. The exercise program consists of 16 exercises per session, varied on the four-letter words chosen at a time. At each session, a combination of four words will be performed and modified weekly. All children will follow the same word combination every week. The exercise program will last 25 to 30 min per session.

The exercise workload will be equal to 60–75% of the maximum heart rate (HR) [20]. The target heart rate (THR) will be calculated based on the following Karvonen formula [21]:THR = [(HR_max_ − HR_rest_) × % intensity] + HR_rest_

Exercise parameters (heart rate, oxygen saturation) will be measured before and at the end of the exercise program by the parents/guardians attending the session. Dyspnea and leg fatigue will be evaluated using the Dalhousie Pictorial Scale [22]. The exercise program will be delivered and monitored by a pediatric respiratory physiotherapist.

Additionally, children and their parents/caregivers will be granted access to a website (www.fysao.gr) for disease management, including information about common symptoms, nutrition, pharmacological treatment, exercise, and ACT performance. The DHSG will utilize this specifically designed digital interface, the development and structural framework of which have been previously detailed by our research team [17]. To facilitate adherence and longitudinal monitoring, the DHSG will receive automated weekly reminders for ACTs and exercise performance. Through the web portal’s integrated evaluation forms, children can report daily symptomatology and track any clinical fluctuations. All the ACTs and the exercises have been digitized as high-definition videos and images, ensuring asynchronous accessibility for the DHSG. Furthermore, the platform facilitates secure communication, enabling children and their parents/caregivers to communicate with healthcare professionals via integrated email or direct document transmission.

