### 2.9. Sample Size Calculation

Due to the lack of pilot data for this specific population, the effect size was estimated a priori. We targeted a moderate effect size (f = 0.25), assuming that this represents a clinically significant improvement in exercise capacity for children with CSLDs. The required sample size was calculated with G*Power version 3.1.9.4 (G*Power, University of Düsseldorf, Düsseldorf, Germany). The “F-test” (ANOVA: repeated measures, within-between interaction) and the detection of a moderate effect size f = 0.25 (alpha level = 0.05, power = 80%) showed that a total of twenty-eight children are required. Assuming a dropout rate of 10%, the total sample size is estimated at thirty-two children, with sixteen in each group.

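### Simple 1:1 randomisation of 32 children is unlikely to give the planned sixteen per group and leaves age balance to chance; age-stratified blocks would be a cheap improvement.

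*Protocol article*

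**What the plan says.** Section 2.1 describes a "prospective, single-center, two-arm (1:1), assessor-blinded, randomized controlled clinical trial that aims to recruit 32 children". Section 2.2 names the method as "1:1 simple randomization". An external person generates the list and prepares opaque envelopes; no blocking, stratification or minimisation is named. The same section says that participants cannot be blinded.

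Section 2.9 concludes that "the total sample size is estimated at thirty-two children, with sixteen in each group".

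Eligible children are 6 to 12 years old (sections 2.3 and 2.4). In the intervention description (section 2.5.1), "the exercises have been modified for two age groups: 6–9 and 10–12 years old". Section 2.10 analyses the outcomes with a 2 × 3 mixed ANOVA in group and time; age is not named as a factor or covariate.

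**The concern.** Section 2.2 makes a definite choice of method, so this is not a detail left to a fuller document, and it sits awkwardly with the equal arms in section 2.9. Simple randomisation gives equal arms only in expectation. With 32 children, visible departures are common.

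The same holds for age. The article treats age as relevant to physical capability: it adapts the exercises to two age bands and sets the step heights of the Chester step test by age (section 2.8.2). It is a reasonable inference that shuttle distance also varies with age over 6 to 12 years, though the article does not say so. Nothing in the allocation protects against one arm being older. At stake are some precision and how readily a result on the modified shuttle walk test could be questioned because of a visible baseline difference. Allocation cannot be repaired once enrolment has begun.

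**Working it through.** **Reproducing the planned size.** Inputs from sections 2.9 and 2.10: f = 0.25, alpha 0.05, power 80%, two groups, three time points, test "ANOVA: repeated measures, within-between interaction". Assumed because not stated: correlation between repeated measures ρ = 0.5, and sphericity. The noncentrality is λ = f² × N × m / (1 − ρ), with (k − 1)(m − 1) and (N − k)(m − 1) degrees of freedom, where k = 2 groups and m = 3 time points.

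- N = 28: λ = 0.0625 × 28 × 3 / 0.5 = 10.5; df 2 and 52; power 81.2%. N = 26 gives 77.8%. The stated 28 is reproduced.
- Dropout: 28 / 0.9 = 31.1, rounded up to 32 for equal arms. The stated 32 is reproduced.

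**Chance of each split.** The size of one arm is binomial (32, ½).

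- Exactly 16:16: C(32,16) / 2³² = 601,080,390 / 4,294,967,296 = 14.0%.
- 19:13 or worse: 37.7%. 20:12 or worse: 21.5%. 22:10 or worse: 5.0%.

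**Cost of unequal arms at N = 32, before dropout.** With 16:16, λ = 0.0625 × 32 × 3 / 0.5 = 12. For arms n₁ and n₂, λ is multiplied by 4n₁n₂ / N². The variance ratio is (1/n₁ + 1/n₂) / (2/16).

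| Split | λ factor | Variance ratio | Power |
|---|---|---|---|
| 16:16 | 1.000 | 1.000 | 86.6% |
| 20:12 | 0.938 | 1.067 | 84.2% |
| 22:10 | 0.859 | 1.164 | 80.7% |

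Averaged over all splits under simple randomisation, power at 32 is 85.4%, a loss of about 1 point. At 28 children the average is 79.5% against 81.2% with 14:14, a loss of about 1.7 points.

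**Age.** The article gives no age distribution, so ages are assumed uniform from 6 to under 13 years (SD 7/√12 = 2.02 years). In 200,000 simulated trials under simple randomisation, the difference in mean age between arms has SD 0.73 years and reaches at least one year in 16.9% of trials. Forcing 16:16 without stratification barely helps (16.2%). If 18 children are aged 6–9 and 14 are aged 10–12, the share in the younger band differs between arms by at least 20 percentage points in about 25% of trials.

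**What restricted randomisation gives.** Same age assumption, strata 6–9 and 10–12, randomly varying blocks. Guessable means the percentage of allocations guessed correctly by someone who knows all past allocations and always guesses the arm that is behind in that stratum. The block rows come from 40,000 simulated trials each.

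| Scheme | Age gap ≥ 1 year | 16:16 or 17:15 | Exactly 16:16 | Guessable |
|---|---|---|---|---|
| Simple | about 17% | 40.3% (100 − 59.7) | 14.0% | 50% |
| Blocks 2 and 4 | about 1% | 99.7% | about 65% | about 71% |
| Blocks 4 and 6 | about 1% | about 98% | about 55% | about 68% |

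**The case against.** The strongest defence is that simple randomisation is valid and unbiased, and is the least predictable scheme available. Sixteen per group can be read as a planning figure, the expected split under 1:1 allocation, and nothing in section 2.10 requires equal arms. Under the stated assumptions even a 22:10 split, reached or exceeded only 5% of the time, keeps power above 80% before dropout. All of this stands.

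The age argument is also limited by the planned test. Baseline is one level of time, so a baseline difference in distance that comes from age drops out of the group-by-time interaction. What remains is the possibility that age affects change. That is plausible, because the exercises differ by age band and children grow over the roughly nine months from baseline to follow-up (12 weeks plus six months, section 2.7). The article neither states nor quantifies it. Section 2.8.1 also compares shuttle performance with a published equation, but its terms are not shown.

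Restricted randomisation has a real price. This is a single-centre trial with unblinded participants, and blocks make the next allocation easier to guess. Small blocks are the worst in this respect, which is why size 2 should be avoided. Stratified blocks do not guarantee 16:16 either, because the last block in each stratum may be incomplete.

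A reader might infer that the trial cannot reach sixteen per group, that the arms will differ in age, or that the primary comparison is biased or underpowered. The documents support none of these. Exact equality is unlikely rather than excluded, age is left to chance rather than certain to be unbalanced, and the average power loss is 1 to 2 points.

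**Conclusion.** The point holds as a cheap improvement, not as an error that invalidates the trial. Sections 2.2 and 2.9 fit poorly: the chosen method misses exactly sixteen per group 86.0% of the time. The probabilities of the splits are exact. The power figures rest on ρ = 0.5 and sphericity, which the article does not state but which reproduce its 28. The age figures rest on an assumed uniform age distribution. The main gain from changing the method is age balance, with the risk of a one-year gap falling from about 17% to about 1%; the gain in power is minor. How much age balance matters to the primary test depends on whether age affects change in shuttle distance, which the article leaves open.

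**What to change.** Before the list is generated, replace simple randomisation in section 2.2 with permuted blocks of randomly varying size that avoid size 2 (for example 4 and 6), stratified by the existing bands 6–9 and 10–12 years. The same external person can produce the list and keep the opaque envelopes; block sizes should be known to that person only. In section 2.9, describe the target as about sixteen per group. If age band enters the primary model, include its interaction with time: a between-child main effect alone would not change the group-by-time test.

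The cost is a different call in the randomisation software and a few words in two sections. The downside is greater predictability than simple randomisation, limited by the concealed block sizes and the envelopes.

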### 2.3. Study Population

The study population consists of children aged 6 to 12 years old with CSLDs other than CF. Specifically, the inclusion criteria will target the diagnostic subgroups of PCD, PBB, and NCFB. Written informed consent will be obtained from all the children and their parents or legal guardians.

### 2.4. Eligibility Criteria

Eligible children will be screened based on a diagnosis of PCD, PBB, and NCFB, established via medical history, clinical features, or/and computed tomography and bronchoscopy findings. Inclusion criteria require children to be aged 6 to 12 years old, clinically stable with an absence of pulmonary exacerbation four weeks before the study’s recruitment, and maintain adherence to attending regular medical follow-up from a pediatric pulmonologist every three months. Regarding the diagnostic scope, children with cystic fibrosis will be excluded. Furthermore, children with immunodeficiency or asthma as their primary condition will also not be included. Additional exclusion criteria include children with clinical evidence of cardiovascular, neuromuscular, metastatic, or psychiatric comorbidities, and neuromuscular or musculoskeletal impairments that affect mobility and the ability to follow instructions. Ineligible children will also include those who have a medical history of lung transplants, who participate in other rehabilitation programs or attend regular physiotherapy ACT sessions (>10 sessions in a 3-month period), lack access to the internet (e.g., no smartphone, tablet, or laptop), or children and/or caregivers who are unable to use technological devices.

### 2.5. Procedure

#### 2.5.1. Intervention

##### Digital Health Services Group (DHSG)

Children randomized to the DHSG will engage in a home-based hybrid (synchronous and asynchronous), remotely administered exercise program and ACTs for 12 weeks. The prescribed weekly regimen will consist of 50 min remote sessions: two synchronous, supervised sessions conducted via the Vsee platform, and a minimum of one asynchronous, unsupervised session. Children will be encouraged to maintain daily adherence to the exercise protocol.

Secure access to the VSee platform will be granted through a unique identification code assigned to each child. Parents/guardians will receive written and verbal instructions regarding the Vsee platform setup, the equipment’s proper use, and safety procedures, including “actions in an emergency” in case of adverse events or technical issues. Adverse events are defined as unintended injuries or clinical incidents resulting from study participation. These include complications such as paroxysmal cough, severe dyspnea, oxygen desaturation (4% drop in SpO_2_), musculoskeletal injury, or loss of balance. To ensure safety in any adverse event (e.g., falls, injury, etc.), at least one parent or guardian will be required to be present in person with the child during sessions. Additionally, written first-aid advice will be given. All adverse events will be recorded during the synchronous videoconferencing sessions. The physiotherapist will document the nature, severity, and duration of each event in a standardized log.

Children will perform ACTs (including individualized teaching and review of postural drainage, percussion, vibration, ACT devices, huffing, coughing), diaphragmatic breathing, and blowing games to enhance mucus expectoration. Both children and parents will be taught how to perform these techniques. During the synchronous, supervised videoconference sessions, the DHSG will be monitored/supervised by the pediatric respiratory physiotherapist for the proper performance of ACTs (device or non-device). All children will perform ACTs once a day for ten minutes. In case of mucus excess, they will be suggested to increase the performance to twice a day. ACTs will be chosen based on children’s ability to use/cooperate and preferences.

Building upon a previous study in children with CF [11], our research team designed an exercise program based on the 24-letter Greek alphabet, where each letter represents an individual aerobic or strengthening exercise, selected so that they can be implemented easily in an online setting at home with minimal equipment. For example, the Greek letter “A” represents the exercise “ALMA”, meaning jumping up and down. In order to adapt the exercise program to age-specific needs and capabilities, the exercises have been modified for two age groups: 6–9 and 10–12 years old. The exercise program consists of 16 exercises per session, varied on the four-letter words chosen at a time. At each session, a combination of four words will be performed and modified weekly. All children will follow the same word combination every week. The exercise program will last 25 to 30 min per session.

The exercise workload will be equal to 60–75% of the maximum heart rate (HR) [20]. The target heart rate (THR) will be calculated based on the following Karvonen formula [21]:THR = [(HR_max_ − HR_rest_) × % intensity] + HR_rest_

Exercise parameters (heart rate, oxygen saturation) will be measured before and at the end of the exercise program by the parents/guardians attending the session. Dyspnea and leg fatigue will be evaluated using the Dalhousie Pictorial Scale [22]. The exercise program will be delivered and monitored by a pediatric respiratory physiotherapist.

Additionally, children and their parents/caregivers will be granted access to a website (www.fysao.gr) for disease management, including information about common symptoms, nutrition, pharmacological treatment, exercise, and ACT performance. The DHSG will utilize this specifically designed digital interface, the development and structural framework of which have been previously detailed by our research team [17]. To facilitate adherence and longitudinal monitoring, the DHSG will receive automated weekly reminders for ACTs and exercise performance. Through the web portal’s integrated evaluation forms, children can report daily symptomatology and track any clinical fluctuations. All the ACTs and the exercises have been digitized as high-definition videos and images, ensuring asynchronous accessibility for the DHSG. Furthermore, the platform facilitates secure communication, enabling children and their parents/caregivers to communicate with healthcare professionals via integrated email or direct document transmission.

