##### Control Group (CG)

Participants in the control group will receive the usual care, typically comprising inhaled antibiotics and/or bronchodilators for respiratory infections as regular pharmacological treatment in clinically stable condition and a 40 min, in-person, physiotherapy session where they will be taught ACTs to perform at home. A printed copy of a handbook, including information on their disease and symptoms, nutrition, pharmacological treatment, exercise, and how to perform ACTs, will be provided.

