### 2.7. Assessment Procedure

All outcome measures will be assessed at the following time points: baseline (before the intervention), the end of the intervention (12 weeks), and follow-up (6 months after the intervention has ended). Assessment procedures will be performed in person at the hospital by a blinded, independent assessor (physiotherapist) on two consecutive days to avoid participant fatigue. Anthropometric characteristics, including weight, height (to calculate body mass index, BMI), fat mass (kg and %), and fat-free mass, will be measured using a stadiometer and the digital fat mass scale TANITA RD-545 (Tanita Corporation, Tokyo, Japan). Pulmonary function will be assessed through the performance of spirometry (Jaeger Vyntus Pneumo, Vyaire Medical, Mettawa, IL, USA) and the forced oscillation technique (FOT) (Jaeger Vyntus IOS, Vyaire Medical, Mettawa, IL, USA) [23,24]. Functional and exercise capacity will be assessed using the 6-minute walking test, the modified shuttle walk test, and the Chester step test. Respiratory muscle strength, handgrip, health-related quality of life (HRQoL), cough-specific QoL, physical activity (PA), and sedentary behavior will be assessed. Furthermore, twice a month for both groups, ACT performance and symptom behavior will be recorded in a detailed diary.

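### The stated adverse-event rule rests on the intervention arm's video sessions and on prior attribution to the study, so ascertainment of harms differs by arm

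*Protocol article*

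**What the plan says.** The only adverse-event text in the Protocol article is in section 2.5.1, under the heading for the DHSG. It contains three statements:

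- Definition: "Adverse events are defined as unintended injuries or clinical incidents resulting from study participation". The examples that follow are coughing fits, marked breathlessness, a fall in oxygen saturation, musculoskeletal injury and loss of balance.
- Occasion: "All adverse events will be recorded during the synchronous videoconferencing sessions".
- Documentation: "The physiotherapist will document the nature, severity, and duration of each event in a standardized log".

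The same section sets the weekly programme as "two synchronous, supervised sessions conducted via the Vsee platform, and a minimum of one asynchronous, unsupervised session", and adds: "Children will be encouraged to maintain daily adherence to the exercise protocol". Airway clearance is also done daily at home.

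Under the Control Group heading, the control arm gets usual care, a handbook and "a 40 min, in-person, physiotherapy session where they will be taught ACTs to perform at home". No video sessions and no adverse-event procedure are described there. Section 2.7 says that "twice a month for both groups, ACT performance and symptom behavior will be recorded in a detailed diary". Section 2.8.1 gives the diary's content as weekly symptoms and the type, frequency and duration of airway clearance. Table 1 has no adverse-event row.

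**The concern.** This is a stated rule, not a silence that a fuller protocol could be expected to fill. The article says what counts as an event, when events are recorded and who logs them. The occasion it names exists in one arm only and covers part of that arm's exposure. The definition also asks for a causal judgement before an event qualifies, so an exacerbation or injury judged unrelated need never enter the log, and that judgement cannot be revisited later. The allocation is open to families and to the treating physiotherapist, so the judgement may differ by arm.

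At stake is what the trial can say about the safety of partly unsupervised home exercise in children aged 6 to 12. A table of events by arm built on this rule would reflect the recording scheme as much as the intervention. The efficacy estimates and the sample size are not affected.

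**Working it through.** The plan gives no figure of its own on this point, so there is none to reproduce. The check sets each source of exposure beside its stated recording route and counts the sessions.

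**Inputs.** From section 2.5.1: "remotely administered exercise program and ACTs for 12 weeks", with 2 synchronous sessions and at least 1 asynchronous session a week. From section 2.9: 16 children per group. From sections 2.7, 2.8.1 and 2.8.2: three in-person assessments, with the modified shuttle walk test and the Chester step test each done twice.

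**Session counts in the DHSG, per child**

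- Synchronous: 2 × 12 = 24.
- Minimum prescription: (2 + 1) × 12 = 36. Unsupervised: 36 − 24 = 12, and 12/36 = 33%. Across the arm: 12 × 16 = 192.
- Upper end, if every child exercised on all days as encouraged: 7 × 12 = 84. Unsupervised: 84 − 24 = 60, and 60/84 = 71%.

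**Maximal exercise tests at the clinic, per child, both arms:** 2 tests × 2 performances × 3 assessments = 12.

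**Stated adverse-event route by setting**

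| Setting | DHSG | Control |
|---|---|---|
| Video sessions | Yes, physiotherapist's log | No such sessions |
| Unsupervised home exercise and airway clearance | No enquiry stated | None stated |
| In-person exercise tests | None stated | None stated |
| 6 months after the intervention | None stated | None stated |

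**Definition against occasion.** An injury during a clinic exercise test plainly results from study participation and so meets the definition. It does not arise in a video session, and in the control arm there is no later video session at which to log it. The two sentences do not fit together for this case.

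**Other channels.** The twice-monthly diary covers both arms, but section 2.8.1 presents it as a compliance measure and names no adverse-event item. The portal described in section 2.5.1 takes daily symptom reports and messages, but only from the DHSG. Neither is tied to the log or asks for nature, severity and duration.

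**The case against.** The strongest reply is that the sentence on recording names an occasion and does not exclude anything. The physiotherapist meets each DHSG family twice a week and could log whatever happened since the last contact; the word all fits that reading. A parent or guardian must be present during sessions and is instructed on emergencies. The DHSG portal takes daily symptoms, the control arm's diary is completed in a physiotherapist's phone call, every child must be under three-monthly specialist follow-up, and both arms attend in person at 12 weeks and at follow-up. Safety is not a stated objective or outcome. At 16 per arm, any comparison of harms would be imprecise: if, as an assumption, 10% to 30% of children had one event, that is 16 × 0.1 = 1.6 to 16 × 0.3 = 4.8 events per arm.

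Much of this stands. A reader might infer that events are recorded in video sessions and nowhere else, so that everything in unsupervised sessions and in the control arm is lost. The text does not say that. Nor can 33% or 71% be read as the share of events missed: they are shares of sessions outside video calls, and the 71% supposes full daily exercise, which is encouraged and not prescribed. A descriptive account of events in supervised sessions would remain valid.

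What does not stand is that these channels close the gap. Logging at the next video session is not stated, and even if done it would leave out the control arm, the clinic tests in that arm, and the follow-up period. The symptom channels are not adverse-event routes, and the portal, being in one arm, widens the difference between arms.

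**Conclusion.** The point holds as a difference in ascertainment. As written, the one stated adverse-event route belongs to the DHSG and requires attribution to the study before an event counts. Harms cannot be validly compared between arms on that basis, and events outside supervised sessions may be under-counted. The extent of under-counting cannot be worked out from the article. What can be counted is exposure outside video calls: at least 12 of 36 prescribed sessions per DHSG child, or 192 across 16 children, plus 12 maximal exercise tests per child in both arms.

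This rests on the article being a fair statement of the rule and on there being no separate adverse-event procedure elsewhere. It does not support a claim of zero capture in the control arm or in follow-up, because the diary and visits may bring some events to light. The change should be made, but it does not threaten the primary analysis.

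**What to change.** 1. Define an adverse event as any untoward event during the trial, whatever its suspected cause. Judge relatedness afterwards and record it as a separate field.
2. Add one short event question set (falls or injury, breathing events, exacerbation, unplanned care) to the twice-monthly diary contact and to the 12-week and follow-up visits, with identical wording in both arms. State whether the diary continues after week 12. If it does not, the follow-up visit must cover the whole interval by recall.
3. In the DHSG, ask at each video session about events since the last contact, and mark each event as supervised or unsupervised.
4. Log events during the clinic exercise tests in both arms.
5. Report counts descriptively by arm, based on the enquiry common to both arms. Show events found only through video sessions separately, since 24 extra contacts in one arm would otherwise bring back the imbalance.

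The cost is a few items on contacts that already take place, slightly longer contacts and more events to log. Two practical points remain. The diary is completed on the website in the DHSG and by phone in the control group, so the mode of enquiry should be aligned or the difference acknowledged. At visits, the questions should be put by someone other than the blinded assessor, because the answers may reveal allocation. Sample size, visits and intervention are unchanged.
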